### Measures

The primary outcome is disability in personal and social functioning (henceforth referred to as *functioning*). Functioning is measured using the World Health Organization Disability Assessment Schedule 2.0 (WHODAS 2.0), which is directly linked to the International Classification of Functioning, Disability and Health [6,7]. According to the World Health Organization (WHO), the concept of disability refers to a degree of functional impairment at the bodily, social, and environmental levels, affecting everyday activities and social participation. WHODAS produces standardized disability levels, which are applicable across all diseases, including mental, behavioral, and neurological disorders, in both clinical and general population settings and across cultures. It captures a person’s functioning in the following six life domains: (1) *cognition*, understanding and communicating; (2) *mobility*, moving and getting around; (3) *self-care*, attending to one’s hygiene, dressing, eating, and staying alone; (4) *getting along*, interacting with other people; (5) *life activities*, domestic responsibilities, leisure, work, and school; and (6) *participation*, joining in community activities and participating in society. The full version of the WHODAS has 36 items. Each item is scored on a 5-point Likert disability scale (0, none; 1, mild; 2, moderate; 3, severe; and 4, extreme). The scores can be summed into an overall functional disability score or presented as six domain-specific sum scores. Alternatively, a more complex scoring algorithm (based on item-response theory) is used (available for SPSS [IBM Corp, Armonk, New York, USA]), which provides an overall score for global functioning on a scale between 0 and 100. In this study, the 36-item self-reported version will be used as a self-administered questionnaire, but trained and supervised interviewers will be available to assist the patients filling in the WHODAS if required. The WHODAS has good psychometric properties and has been designed to monitor the impacts of health and health-related interventions, with a Cronbach α of .86 (range .82-.98) [7].

The secondary patient-level outcome is health-related quality of life, which will be measured using the three-level EuroQoL five dimensions (EQ-5D-3L) [8], which is more commonly used in Eastern Europe. Moreover, a translated version of the newer five-level scale is not available for all countries at the start of the study. The EQ-5D-3L contains the following five dimensions of health-related quality of life: mobility, self-care, daily activities, pain or discomfort, and depression or anxiety. Each dimension can be rated at three levels (from no problems to major problems). The five dimensions can be summed into a descriptive health state with “11111” indicating no problems in any of the five health dimensions and “33333” indicating major problems in all dimensions. In this way, the EQ-5D-3L can describe 243 (3^5^) health states. For each of the health states, utility values can be calculated using health state preferences elicited from the Slovenian population [9], as no health state preferences are currently available for any of the five countries included in this study, and out of the available countries, Slovenia is chosen owing to its geographical proximity, as well as similar historical and social environment. For the purpose of sensitivity analyses, utility values will also be elicited using the EuroQoL visual analog scale (VAS). The utility values give weight to the amount of time that a person spends in a certain health state, which is used to compute QALYs. In the CUA, the QALYs will be the outcome of interest.

Data on *resource use* (healthcare uptake, including informal care, travel distances to health services, and productivity losses stemming from functional impairment) will be collected using an adapted version of the Trimbos/iMTA Questionnaire on Costs associated with Psychiatric illness (TiC-P) [10]. We will consider the following three types of costs: (1) health care costs; (2) out-of-pocket costs (from patients and their family members for travel and informal care); and (3) costs stemming from productivity losses due to absenteeism and lesser efficiency while at work (presenteeism). Costs will be estimated using a bottom-up (or microcosting) approach, where units of health service are multiplied by their appropriate unit cost price and summed to provide an overall total cost estimate [11]. Costs will be measured in the local currency, but for the economic evaluation, they will be converted to international euro (Int.€) using purchasing power parity that takes into account exchange rates and the respective buying power in the countries. The reference year for the costs will be 2018.

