### Randomization and Masking

Eligible and consenting patients will be randomly allocated to either the intervention (receiving care provided by CMHTs) or usual care condition consisting of inpatient or outpatient mental health care (described above). An independent statistician, otherwise not involved in the trial, will carry out the randomization at each of the sites, with patients as the unit of randomization. Simple randomization with 1:1 allocation will be applied using a randomization website [5] for true random number generation. In this type of study (a hybrid implementation-effectiveness trial), it is not possible to conceal the randomization status from either clinicians or patients, and masking will therefore not be attempted.

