## Discussion

### General Considerations

This study will examine the cost-effectiveness of recovery-oriented community mental health care for patients with severe mental disorders (the intervention implemented in the RECOVER-E project) compared with CAU in Bulgaria, Croatia, Macedonia, Montenegro, and Romania. Health-economic evaluations will be conducted alongside hybrid effectiveness-implementation trials at each of the five sites. In addition, a pooled analysis will be performed combining all trial data. It is hypothesized that the shift toward deinstitutionalization using a locally adapted form of flexible assertive community treatment results in the reduction of health care costs by avoiding expensive emergency care or psychiatric hospitalization. At the same time, this intervention has a focus within service delivery on recovery goals, which is hypothesized to contribute to a greater sense of societal role fulfilment and participation in society among people with severe mental illness. It is not unlikely that patients receiving community care will show larger improvements in WHODAS personal and social functioning and EQ-5D health-related quality of life as compared with patients treated in hospital-based mental health care services.

Given the nature of the intervention, a pragmatic approach is chosen to implement and evaluate community mental health services. While this may affect internal validity (eg, due to the lack of allocation concealment and masking), the corresponding results may be more generalizable and applicable to routine practice settings [31]. Moreover, the proposed methodology includes some methodological solutions to combat threats to the internal validity of the trials (eg, inverse propensity score weighting when randomization appears to be suboptimal).

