There are additional limitations that are anticipated and worth noting. Among these, the lack of country-specific EQ-5D tariffs and the difficulty to obtain unit cost prices in lieu of national standard cost prices are relatively important. In an effort to address this lack of tariffs and standard cost prices, the EQ-5D VAS will be used to obtain QALYs and the microcosting technique will be used to obtain reasonably accurate local cost prices. Nonetheless, these approaches may introduce bias in the QALY and cost estimates. It is hoped that these biases occur to the same degree in the CMHC condition as in the CAU condition of the trials and will therefore cancel each other out when computing cost differences and effect differences across the conditions. Moreover, robust statistical techniques will be used, such as nonparametric bootstrapping and inverse propensity score matching. Furthermore, the main analysis will be subject to various sensitivity analyses precisely directed at uncertainties in costs and outcomes in order to ascertain the robustness of the main analysis.

The use of the WHODAS self-report version instead of the interviewer-administered version may cause some reporting bias (eg, due to differences in the literacy level between participants). However, given the randomized nature of the study, we expect this bias to be present equally in both arms. Furthermore, the self-reported version of the WHODAS has been demonstrated to identify improvements in functioning following treatment in people who have certain health conditions (eg, depression, schizophrenia, and alcohol problems) [7]. Regarding the use of the EQ-5D-3L, there is some evidence demonstrating a lack of responsiveness in patients with schizophrenia [32]. However, the EQ-5D-3L is recommended as the preferred utility instrument in most countries worldwide, and in line with the recommendations of Payakachat et al [32], we believe that an appropriate estimate of effectiveness is ensured by also using the WHODAS.

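### The reason given for dropping all masking does not cover the interviewers who help patients complete the primary-outcome WHODAS, and the stated safeguards do not reach bias arising after allocation

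*Protocol article*

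**What the plan says.** All references are to the protocol article.

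- **Outcome and mode (Methods, Measures).** "The primary outcome is disability in personal and social functioning", measured with the WHODAS 2.0. On administration, "the 36-item self-reported version will be used as a self-administered questionnaire", and "trained and supervised interviewers will be available to assist the patients filling in the WHODAS if required". The article gives no criterion for when help is needed.
- **Masking (Methods, Randomization and Masking).** The article says that "it is not possible to conceal the randomization status from either clinicians or patients, and masking will therefore not be attempted". Interviewers are not mentioned.
- **Timing (Methods, Design).** Assessments are at baseline, 12 months and 18 months. The two follow-ups necessarily come after allocation is known. Whether the baseline WHODAS is completed before or after allocation is not stated.
- **Acknowledged limits (Discussion, General Considerations).** On the pragmatic design: "While this may affect internal validity (eg, due to the lack of allocation concealment and masking"). The example of a solution is "inverse propensity score weighting when randomization appears to be suboptimal". On choosing self-report over interview, the article says that this "may cause some reporting bias (eg, due to differences in the literacy level between participants"), and then: "given the randomized nature of the study, we expect this bias to be present equally in both arms".

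**The concern.** The outcome is a subjective report, allocation is open, and a third party may help with the form at the visits that supply the treatment comparison. A helper who knows the allocation can influence how items are explained or answered, and known allocation can influence who asks for help. If either differs by arm, the difference enters the WHODAS contrast and cannot be told apart from a treatment effect.

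The decision not to mask goes further than its premise. That patients and treating clinicians cannot be masked is a sound observation about this intervention. It does not follow that the staff who help with a questionnaire cannot be kept unaware of allocation, or separate from the treating teams.

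Neither statement in the Discussion closes the gap. Weighting by a propensity score acts on baseline covariates, not on how the outcome was obtained a year later. Randomization balances literacy in expectation, but it does not balance influences that begin after allocation.

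The cost-effectiveness analysis is exposed too. Response is an improvement of 6 points or more, so an arm difference in how the form is completed could move patients across that threshold.

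**Working it through.** **1. What each stated safeguard reaches**

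| Statement | What it covers | What it leaves open |
|---|---|---|
| Masking infeasible for clinicians and patients | Treating staff and participants | Staff who assist with the WHODAS |
| Inverse propensity weighting | Imbalance in baseline variables | Measurement bias arising after allocation |
| Equal bias because of randomization | Traits fixed before allocation, such as literacy | Help or reporting influenced by known allocation |

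No statement in the article reaches assistance at 12 and 18 months.

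**2. The plan's own sample size, as the basis for scale**

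Inputs from Sample Size Calculation: d = 0.33, two-sided α = 0.05, power 0.80, 90 per arm, r01 from 0.3 to 0.5, r12 from 0.2 to 0.4. For ANCOVA with one baseline and two follow-ups:

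n per arm = 2 × ((z0.975 + z0.80)/0.33)² × [(1 + r12)/2 − r01²]

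The first factor is 144.15. With r01 = 0.3 and r12 = 0.4 the bracket is 0.70 − 0.09 = 0.61, and 144.15 × 0.61 = 87.9, which rounds up to 88, as in Table 1. All nine cells of Table 1 reproduce, so the sample size is not in question. Cost-Effectiveness Analysis equates 0.33 standard units with 6 points, so the implied SD is 6/0.33 = 18.2 points.

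**3. Effect of an assumed between-arm bias b (SD units), with no true effect**

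SE = √f × √(2/n), with f the bracket above.

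Rejection rate = 1 − Φ(1.96 − b/SE) + Φ(−1.96 − b/SE)

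Example: f = 0.61 and n = 90 give SE = 0.781 × 0.149 = 0.116. For b = 0.10, b/SE = 0.86, and the rate is 13.8%.

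| Assumed b | Points | 90 per arm, r01 = 0.3, r12 = 0.4 | 90 per arm, r01 = 0.5, r12 = 0.2 | Pooled, 450 per arm, r01 = 0.3, r12 = 0.4 |
|---|---|---|---|---|
| 0 | 0 | 5.0% | 5.0% | 5.0% |
| 0.05 | 0.9 | 7.1% | 8.8% | 16% |
| 0.10 | 1.8 | 13.8% | 20.5% | 48% |
| 0.15 | 2.7 | 25.1% | 39.8% | 82% |
| 0.20 | 3.6 | 40.4% | 62.1% | 97% |

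The pooled column ignores site effects and assumes the same bias at every site. Pooling does not remove a shared bias; it makes a false-positive result more likely.

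**4. One route to such a bias, with assumed inputs**

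Bias in points = (arm difference in the share assisted) × (score shift due to assistance). With assumed differences of 10 to 30 percentage points and assumed shifts of 3 to 8 points, the range is 0.1 × 3 = 0.3 to 0.3 × 8 = 2.4 points, which is 5% to 40% of the 6-point target.

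For the responder outcome, SD of change = 18.2 × √(2(1 − r)), which is 21.5 at r = 0.3 and 18.2 at r = 0.5. With a true mean improvement of 0 or 6 points, a 3 to 8 point shift moves the response probability of one patient whose mode changes by about 5 to 17 percentage points. Multiplied by the same 10 to 30% difference in assistance, this is about 0.5 to 5 percentage points at arm level.

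**The case against.** **A stronger reading is tempting and not supported.**

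- A reader might infer that the plan claims all reporting bias is equal across arms. It does not. The sentence refers back to the choice of self-report over interview, with literacy as the example, and for that it is reasonable. It is incomplete as a general reassurance, not wrong as written.
- A reader might infer that unmasked community-team members help with the form, perhaps at home visits. The article says only that the interviewers are trained and supervised. That they are unmasked follows from the blanket no-masking statement. That they belong to a care team, or that assistance differs by arm, is stated nowhere.
- A reader might infer that open allocation was overlooked. The Discussion names lack of masking as a possible threat to internal validity and presents it as a price of the pragmatic design.

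**Condensation.** Data Handling refers to a central study protocol and local versions. Who the interviewers are and what the form records may be set out there, so their absence from the article is no fault. What the article does state is a no-masking rule whose reason is narrower than its scope, and that part stands.

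**Size and effect of a remedy.** The bias sizes are assumptions, and help that is equal in both arms would not bias the mean difference. Masking helpers also leaves the larger exposure in place, because the patient is the rater and knows the allocation. Both points are correct. They limit what the change can achieve but do not justify leaving assisting staff out.

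**Conclusion.** The point holds in a limited form. The article abandons all masking for a reason that does not extend to the interviewers who assist with the primary outcome after open allocation. The remedy it names addresses baseline imbalance only, and its expectation of equal bias reaches only traits fixed before allocation.

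The documents do not establish that bias will occur, its direction or its size. The error rates above are conditional on an assumed bias. They show that even 1.8 points, less than a third of the 6-point target, would matter at 90 per arm and more so in the pooled set. The sample size is unaffected. This is an inexpensive improvement to the design and wording, not a defect that invalidates the trials.

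**What to change.** 1. **Randomization and Masking, and Measures.** State that for all remaining assessments, where feasible, the already planned interviewers who assist with the WHODAS are not members of the community team or the treating usual-care staff and are not told the allocation, and that patients are asked not to reveal it.
2. **Measures.** Record for each WHODAS whether it was self-completed or assisted, and report this by arm and visit.
3. **Discussion, General Considerations.** Limit the equal-bias sentence to baseline traits such as literacy, and say that help or reporting after allocation may differ by arm.

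Two further steps may look natural but should be avoided. Restricting an analysis to participants with the same mode at every visit selects on something decided after allocation and departs from the intention-to-treat set. Obliging participants to keep their baseline mode could produce missing data when someone later needs help. If mode is explored, do so descriptively or by baseline mode, keeping the full randomized set.

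**Cost.** Some scheduling effort and one form field, with no new staff. Patients will occasionally reveal their allocation. The Results section reports 91 + 165 + 180 + 197 + 190 = 823 participants already included, so mode may be unrecorded for assessments already done. The patient as rater remains unmasked, so the bias is reduced and not removed.

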### Data Handling

Data will be handled in accordance with the General Data Protection Regulation [12]. A central Study Protocol and Data Management Plan coordinates all of the five independent trials. In addition, each trial will have a data entry template, a locally adapted version of the study protocol, and a locally adapted version of the central project data safety and management plan.

### Sample Size Calculation

Each of the trials is well powered with 90 participants per randomization group (n=180 in total) to detect a clinically relevant effect (mean standardized difference, *d*) of ≥0.33 as statistically significant (at α≤.05, two-tailed) with a power (1-β) of ≥0.80 when the primary outcome (WHODAS personal and social functioning) is evaluated in a baseline-adjusted analysis of variance or similarly specified regression model.

More specifically, the power calculation is carried out with the sample size procedure of Stata (Stata Corp, College Station, Texas, USA) (*sampsi* [13]) assuming that the effect evaluation of functioning would be carried out in a baseline-adjusted analysis of covariance (ANCOVA) with one baseline measurement and two follow-ups. We had to make assumptions about the strength of the correlation of functioning between *t_0_* and *t_1_* and between *t_1_* and *t_2_* (denoted as *r_0,1_* and *r_1,2_*, respectively). The WHODAS 2.0 has a high 1-week test-retest reliability of *r_0,1_*=0.98 [14], but the correlation between *t_0_* and *t_1_* will be lower when the measurements are further apart (12-month time interval between *t_0_* and *t_1_*). Hence, we assumed that *r_0,1_* would be in the more modest range of 0.30 to 0.50. Regarding the strength of the correlation of personal and social functioning between *t_1_* and *t_2_*, we made a similar assumption, but expect that this correlation will be weaker still (ie, in the range of 0.20 to 0.40). The size of these correlations is important because they affect the required sample size. For this reason, the sample size calculations were repeated for the likely range of *r_0,1_* and *r_1,2_*. Table 1 shows the required sample size (per arm) for varying *r_0,1_* and *r_1,2_* values.

**Table 1 table1:** Required sample size per condition for varying *r_0,1_* and *r_1,2_* values.

*r_1,2_* ^a^	*r_0,1_* ^b^		
	0.3	0.4	0.5
0.2	74	64	51
0.3	81	71	58
0.4	88	78	65

^a^Correlation of functioning between 12 months after baseline (*t_1_*) and 18 months after baseline (*t_2_*).

^b^Correlation of functioning between baseline (*t_0_*) and 12 months after baseline (*t_1_*).

Table 1 shows that in all possible scenarios, the study would be well powered with 88 participants (say 90 participants per condition or 180 in total). In fact, there is a chance that a smaller participant number would suffice, but it is better to be safe. As indicated, the power is based on the idea that the analyses will be conducted with ANCOVA repeated measures or an equivalently specified linear mixed regression model. It was therefore tested if a total sample size of 180 is sufficient for detecting the effect of *d*≥0.33 as statistically significant at α≤.05 (two-tailed) with a power of 0.80, when mixed modelling is used. Hence, to determine the sample size required to achieve 80% power, 1000 mixed model simulations were performed, in which baseline measurement and a random effect for individuals were considered. In generating the simulation data, correlations of 0.3 and 0.1 (Pearson *r*) were assumed between *t_0_* and *t_1_* and between *t_1_* and *t_2_*, respectively. Furthermore, a treatment effect of 0.33 was assumed. In doing so, a sample size of 180 was found to be sufficient.

We will not compensate for dropout by increasing the number of participants at baseline, unless the local research teams identify additional opportunities to recruit more patients than the minimum of 180. As part of the ITT analysis, all participants will be analyzed as randomized, and this will be achieved by either using mixed modelling or imputing missing observations. Imputation is not only required to persevere randomization integrity, but will in addition restore power losses due to dropout. In summary, local teams will have to recruit 180 participants, but can recruit more (up to a maximum of 200) to compensate for dropout when logistically feasible.

It should be noted that the power analysis is directed at the evaluation of the central clinical end-term functioning (ie, the alternative hypothesis predicts that functioning will be at least 0.33 standard units better in the CMHC condition compared with the CAU condition). It is not customary to power a study for testing a health-economic hypothesis, because the large standard errors associated with costs would require extremely large sample sizes. Instead, in health-economic evaluation, a probabilistic medical decision-making approach is used for making inferences about the relative cost-effectiveness of CMHC compared with CAU.

Finally, it is worth mentioning that both the clinical and health-economic evaluations will be based on the pooled dataset of all 900 participants when the data of all five trials are combined.

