Although the operationalization of the societal perspective is challenging, in this study, we believe the use of the term “societal” is justified, as we include relevant societal costs, such as informal care, travel distances to health services, and productivity losses stemming from functional impairment. However, the educational and criminal justice sectors, which are often overlooked, may also be considered [33]. In this study, we feel that these sectors are relevant to a lesser extent and the substantial efforts in collecting data within these sectors is not justified by the expected impact on total costs (especially for the educational sector as we include adults only).

Lastly, we expect that it will be difficult for some of the participating study sites to recruit 180 participants into the trials and that the trials are likely to experience loss to follow-up. This may deflate the sample size and power. In the event of this occurring, power-efficient statistical techniques will be employed, such as baseline-adjusted ANCOVA (repeated measures) and similarly specified linear mixed models for ITT analysis. It is also worth noting that the economic evaluation will be conducted on the pooled dataset of all five trials combined, which will mitigate power issues, if any.

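### Imputation is wrongly said to restore power lost to dropout, so power of at least 0.80 per trial is not assured once participants are lost

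*Protocol article*

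**What the plan says.** The Sample Size Calculation section states: "Each of the trials is well powered with 90 participants per randomization group". The aim is to detect a standardised difference "of ≥0.33 as statistically significant (at α≤.05, two-tailed) with a power (1-β) of ≥0.80". The calculation assumes ANCOVA on one baseline and two follow-up measurements. The baseline to 12-month correlation (r01) is taken as 0.3 to 0.5 and the 12-month to 18-month correlation (r12) as 0.2 to 0.4. Table 1 gives nine required sizes, from 51 to 88 per arm. The largest, 88, is rounded up to 90, and power is described as adequate for every combination in the table.

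On dropout, the section says: "We will not compensate for dropout by increasing the number of participants at baseline". Sites may go beyond 180, to at most 200, if they find it feasible. Randomised participants are to be kept in the analysis through a mixed model or imputation, and then comes the claim: "Imputation is not only required to persevere randomization integrity, but will in addition restore power losses due to dropout".

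The Discussion (General Considerations) expects recruitment difficulty and loss to follow-up and accepts that both may lower power. It continues: "In the event of this occurring, power-efficient statistical techniques will be employed, such as baseline-adjusted ANCOVA (repeated measures", or a similar mixed model, and adds that pooling the five trials will help.

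**The concern.** Imputed outcomes are generated from the data that were observed. Under missing at random, a sound imputation or mixed model can remove bias. It can also recover some information from a 12-month value or from strong auxiliary variables. It cannot return the full information of outcomes that were never measured.

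The claim matters because it stands in the paragraph that leaves dropout out of the required 180 and is offered there as a remedy. It also sits badly with the Discussion, which accepts that loss to follow-up may reduce power. The Discussion's response, baseline-adjusted ANCOVA or an equivalent mixed model, is the analysis Table 1 already assumes, so its efficiency has been spent.

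Each country's trial is to be reported separately. If the power figure is taken at face value, a null result in one country could be read against a power that the trial did not have.

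**Working it through.** **Inputs.** From the Sample Size Calculation section: d = 0.33, two-sided α = 0.05, power 0.80, 90 per arm, one baseline and two follow-ups, and the correlations above. The documents give no dropout rate, so 10%, 20% and 30% are assumptions.

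**Reproducing Table 1.** With the baseline equally correlated with both follow-ups, the sampsi ANCOVA formula is

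n per arm = 2 × [(1.96 + 0.8416)/0.33]² × F, where F = (1 + r12)/2 − r01².

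The multiplier is 144.15. For r01=0.3 and r12=0.4, F = 0.70 − 0.09 = 0.61, so n = 144.15 × 0.61 = 87.9, which rounds up to 88. All nine cells reproduce exactly.

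**Adding dropout.** If lost participants miss both follow-ups, power = Φ(0.33 × √(n/(2F)) − 1.96), with n the completers per arm. In the worst cell:

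- n = 90 (no loss): 0.809
- n = 81 (10%): 0.767
- n = 72 (20%): 0.717
- n = 63 (30%): 0.660

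The tolerated loss is 1 − 87.9/90 = 2.3% with 90 per arm and 1 − 87.9/100 = 12.1% with 100 per arm.

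| r01 / r12 | n in Table 1 | Power, 90 per arm, 0 / 10 / 20 / 30% loss | Tolerated loss, 90 per arm | Tolerated loss, 100 per arm |
|---|---|---|---|---|
| 0.3 / 0.2 | 74 | 0.873 / 0.837 / 0.792 / 0.737 | 18.3% | 26.5% |
| 0.4 / 0.2 | 64 | 0.916 / 0.886 / 0.847 / 0.797 | 29.5% | 36.6% |
| 0.5 / 0.2 | 51 | 0.963 / 0.944 / 0.917 / 0.879 | 43.9% | 49.5% |
| 0.3 / 0.3 | 81 | 0.841 / 0.801 / 0.754 / 0.697 | 10.3% | 19.3% |
| 0.4 / 0.3 | 71 | 0.885 / 0.851 / 0.807 / 0.754 | 21.5% | 29.4% |
| 0.5 / 0.3 | 58 | 0.938 / 0.913 / 0.879 / 0.834 | 35.9% | 42.3% |
| 0.3 / 0.4 | 88 | 0.809 / 0.767 / 0.717 / 0.660 | 2.3% | 12.1% |
| 0.4 / 0.4 | 78 | 0.854 / 0.815 / 0.769 / 0.712 | 13.5% | 22.2% |
| 0.5 / 0.4 | 65 | 0.910 / 0.879 / 0.839 / 0.788 | 27.9% | 35.1% |

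Power is below 0.80 in 1, 4 and 7 of the nine cells at 10%, 20% and 30% loss.

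**Partial follow-up.** Let x be the proportion lost, half of them still measured at 12 months. Given baseline, each follow-up has variance 1 − 0.09 = 0.91 and the two have covariance 0.4 − 0.09 = 0.31. Someone with both values contributes 2/(0.91 + 0.31) = 1.639 units of information, and someone with the 12-month value only contributes 1/0.91 = 1.099. With I = 90 × [(1 − x) × 1.639 + 0.5x × 1.099], power = Φ(0.33 × √(I/2) − 1.96). This gives 0.782, 0.752 and 0.718 at 10%, 20% and 30%. If every dropout is seen at 12 months, the figures are 0.796, 0.782 and 0.767.

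**Maximum recruitment.** With 100 per arm in the worst cell, power is 0.809 at 10% loss and 0.762 at 20%.

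**Detectable effect.** In the worst cell with 72 completers per arm, d = 2.8016 × √(2 × 0.61/72) = 0.365. With 80 completers per arm (100 less 20%), d = 2.8016 × √(1.22/80) = 0.346.

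**Does the named imputation help?** The Cost-Effectiveness Analysis section specifies single imputation by predictive mean matching inside a bootstrap. This was simulated in the worst cell on the continuous outcome, averaged over the two follow-ups (700 trials, 300 bootstraps each, completely random loss of both follow-ups, treatment arm and baseline score as predictors). Power with imputation against complete-case ANCOVA was 0.81 against 0.79 with no loss, 0.66 against 0.71 at 20%, and 0.57 against 0.64 at 30%. Imputation restored nothing in that setting.

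**The case against.** Several points on the other side stand.

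- A reader might infer that the plan makes no allowance at all for dropout. It does make one: recruitment up to 200 is permitted for that purpose and has been used. The Results section reports 197 participants in Montenegro and 190 in North Macedonia, which in the worst cell tolerate about 10.7% (1 − 175.9/197) and 7.4% (1 − 175.9/190). But the allowance is optional and capped, and Croatia (165) and Bulgaria (91) were below 180 at that time.
- A reader might infer that power of at least 0.80 is simply not achieved. The documents do not support this. Sizing on the worst cell leaves slack elsewhere: the other cells tolerate about 10% to 44% loss. The correlations in the article's own simulation check (0.3 and 0.1) need 67 per arm and still give 0.831 at 20% loss. No dropout rate is stated, so actual power cannot be known.
- A reader might take the Discussion to claim that efficient models fully make up for lost participants. It offers them only as mitigation and admits that power may fall. The narrower point is that they add no reserve beyond Table 1.
- Imputation can recover something. The plan imputes from predictors of outcome and of missingness, and strong auxiliary variables would do better than the simulation above. Partial recovery is still not restoration.
- The economic inference is probabilistic and not powered, and a pooled analysis of 900 is planned. This limits the effect on the article's main question, but pooling does not rescue a power statement made for each trial.

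**Conclusion.** The concern holds in this form: the statement that imputation restores lost power is wrong, the required 180 contains no dropout term, and power of at least 0.80 is not assured over the whole of Table 1 once dropout occurs. Table 1 itself is arithmetically correct; the error lies in the justification for leaving dropout out.

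The shortfall is largest in the cell that fixed the sample size. There the margin is 2 participants per arm, and power falls to about 0.72 at 20% loss of both follow-ups, or about 0.75 if half of those lost are seen at 12 months. In the central cell (0.4, 0.3) power stays at 0.80 up to about 21.5% loss.

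These figures rest on assumed loss rates, equal loss in both arms, a normal approximation and the article's own correlations.

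**What to change.** 1. In the Sample Size Calculation section, delete the claim that imputation restores power. Say instead that imputation and mixed models mainly address bias and recover only part of the lost information.
2. Replace the assurance of adequate power throughout Table 1 with per-trial power and detectable effect by assumed loss (for example 10%, 20% and 30%), at 180 and at 200 participants. For the worst cell at 20% loss, the detectable d is about 0.36 with 90 per arm and about 0.35 with 100 per arm. State whether lost participants are assumed to miss both follow-ups or only the second.
3. In the Discussion, note that baseline-adjusted ANCOVA or the mixed model is already assumed in Table 1 and gives no extra reserve against dropout.

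The cost is a few sentences, one table and a less favourable power figure. No extra participants or data, and no change of analysis, are needed.
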